## Abstract

**Introduction:**

The United States is facing an opioid use disorder (OUD) epidemic, marked by unprecedented overdose death rates. In New York State, synthetic opioids significantly contribute to the increasing overdose deaths, disproportionately impacting Black and Latinx communities. There is an urgent need to address issues related to equitable access to and the quality of care provided by substance use disorder (SUD) treatment programs. In light of this, the Quality Measurement and Management Research Center (QM2-RC) brought together an academic-government partnership to develop a person-centered quality measurement system and to assess its impact on a statewide treatment system that serves approximately 180,000 individuals per year.

**Methods and analysis:**

The QM2-RC encompasses three interconnected projects (Project 1, 2, and 3) aimed at developing a quality management strategy and evaluating its impact on system performance across New York State. This report specifically focuses on Project 3, which involves a stepped-wedge trial with 35 clinics receiving a quality management intervention that includes performance coaching. This intervention will be compared to a treatment-as-usual (TAU) condition for clinics not participating in the trial. Administrative data will be utilized to monitor outcomes over four years. The coaching intervention, guided by the Integrated Promoting Action on Research Implementation in Health Services (i-PARIHS) model, emphasizes interpreting quality measures and applying insights to enhance care. Coaches will provide support on data utilization, patient-centered care, harm reduction strategies, and the use of patient monitoring tools. The trial aims to evaluate clinic staff and leadership attitudes, experiences, and behaviors through surveys, semi-structured interviews, and external facilitator notes. Primary clinic outcomes will be assessed through adverse events, decreased clinic rates of substance use related emergency department visits and hospitalizations as well as mortality among patients within the first 12 months after admission to treatment after adjusting for individual and community level characteristics. This study is being developed over a multi-year period and will be informed by a mixed-methods approach incorporating multiple data sources, qualitative interviews, patient and clinic surveys. The study is being conducted in partnership with New York State Office of Addiction Services and Supports (OASAS) and will be informed by input from patient, providers, health insurers, family members and local governing units.

**Discussion:**

Project 3 of the QM2 study specifically targets key barriers in measuring the quality of SUD treatment, including technological limitations, unvalidated measures, workforce data literacy, and concerns about fairness in assessing clinical complexity. Through the implementation of a stepped-wedge trial involving 35 clinics, the project aims to develop new quality measures, offer performance feedback, and engage clinic leadership and staff in efforts to improve practices. The ultimate goal of Project 3 is to overcome these barriers, promote person-centered care, and improve SUD treatment practices across New York State.

## Introduction

The United States is facing an opioid overdose epidemic, with high overdose rates. In 2021, 107,622 individuals died of an overdose, which is largely associated with increasing range of synthetic substances in the illegal drug supply [1]. New York State in particular is experiencing a marked rise in synthetic opioids and overdose deaths, with nearly 5,000 attributed to opioids in 2021, accounting for approximately 68% of the increase in opioid overdose deaths between 2019 and 2021 [2]. This crisis is disproportionately affecting Black and Latinx individuals, highlighting disparities in the impact of the epidemic on communities of color [3–9]. Black and Latinx people who use drugs (PWUD) have been especially affected by the contamination of other substances with synthetic opioids [8]. The rising overdose rates [10,11] raise important questions about equitable access to treatment and the quality of care for individuals with substance use disorder (SUD) [2], particularly in high-impact areas such as New York state with a high number of opioid use and its consequences including opioid use disorder (OUD) [12–14]. OUD is associated with high morbidity and mortality including overdose death [15–21]. 

SUD treatment programs have the potential to deliver evidence-based interventions, including medication for OUD (MOUD), integrated mental health care, and recovery or supportive services, which can be lifesaving for highly stigmatized individuals such as Black and Latinx PWUD. However, previous systematic reviews have identified deficiencies in the quality of care provided by SUD treatment programs across the United States, as well as limited infrastructure and capacity to support continuous clinical improvement [22–32]. While there is variability in quality across clinics, low treatment retention [24,33–38], limited utilization of evidence-based practice [22,23] (e.g., MOUD), and disregard of patient preferences and perspectives have been widely documented [39–42].

Multiple studies have documented racial and ethnic disparities in quality of care, finding lower retention and poorer outcomes from SUD treatment for Black and Latinx patients compared to non-Latinx White patients [43–53]. Treatment programs located within communities made up predominantly of people of color tend to offer fewer and lower-quality treatment services [54]. Non-Latinx White patients clients are more likely to receive care that matches their needs [43,55]. Indeed, the most obvious reason for racial disparities in treatment outcomes may be that treatment programs are not routinely using evidence-based treatment practices [31,43,51,56–59]. For example, opioid treatment programs (OTPs) that treated a higher percentage of Black clients were more likely to dispense doses that were too low to be effective [60].

Quality measurement and reporting offers a means of holding the treatment system accountable to service users, regulators, and payors and of improving care. Despite continued calls for the development of SUD treatment quality measures, there is a dearth of generally accepted and validated measures to guide measurement and management strategies [22,27,61–63]. The National Quality Forum (NQF) recently convened two expert panels to provide recommendations on measurement development in response to the opioid epidemic [64,65]. The panel called for a quality measurement approach that is aligned with a chronic care approach to SUD/OUD treatment, with an expanded focus on treatment processes including person-centered care, measurement-based care, harm reduction, integrated care for comorbid conditions, and attention to care for special populations that are traditionally underserved, namely pregnant individuals and justice-involved populations.

The creation of actionable and implementable quality measurement and management (QM2) systems in the SUD treatment context have been hampered by three limitations. First, limited access to data and resources required to conduct measure validation has been a major barrier to developing quality measures, as requested by stakeholders [66–68]. As a consequence, SUD quality measures often rely on administrative and/or insurance claims data with a limited amount of data sources. While claims provide a readily available set of clinical data for each healthcare encounter, the billing process introduces delays in data availability, limiting the utility of quality measures for informing current quality improvement efforts [66]. In addition, claims data lack detailed information on the types of practices used for services like mental health counseling and fail to support quality measures based on patient outcomes or experience [69].

Second, SUD treatment programs’ capacities to interpret and use quality measures for clinical care improvement may be limited [22,24–28]. The SUD treatment workforce often lacks adequate education and professional training to effectively implement process change initiatives designed to enhance clinical outcomes [22,26,27,70]. An ideal QM2 study would promote the incorporation of quality measures into a culture of continued learning and adaptation [22,71]. However, limited research exists on how to best guide SUD treatment programs to use learning systems and data-driven quality improvement efforts [72,73] Research has shown that SUD treatment clinics require external support and guidance to adopt system improvement practices [74–78]. Many clinics face significant challenges in adopting these process improvement practices, including the commitment required by staff, scarce resources to implement burdensome processes, detailed data requirements, and issues with long-term sustainability [72,76,79].

Lastly, SUD treatment programs have concerns about the fairness of quality measures. One significant concern is the variability in clinical complexity, which may hinder the ability of programs to deliver consistent levels of care and potentially diminish an individual’s capacity to respond effectively to treatment [80]. Some complexities relate to health status, such as comorbid physical and mental health conditions [81–83]. Other factors affecting clinical client complexity involve social determinants of health at the person level (e.g., low educational attainment, homelessness) and the community within which the patient lives [84–86]. These complexities can create greater barriers to treatment engagement or have distinct effects on outcomes [80,87,88]. Similarly, patients living in communities with large social vulnerabilities face additional challenges that can affect their ability to benefit from treatment [89,90]. Some programs providing treatment for marginalized clients from highly stressed communities may present as performing poorly yet serve a vital role in providing services [91–93]. Consequently, programs advocate for the presentation of quality measures that are adjusted to account for the specific challenges faced by their patients and communities, such as socioeconomic factors, health disparities, and access to care.

The QM2 Study is a five-year NIH-funded center grant consisting of three projects aimed at building and testing an evidence-based QM2 study for person-centered treatment – a collaborative approach to individualized treatment. The first project of QM2 aims to develop and test a new set of quality measures for the substance use treatment system in New York State. The measure constructs will be created in conjunction with stakeholders (e.g., people who use treatment services, clinicians, and payers) to select and refine quality measures that span person-centered care, evidence-based practice, and harm-reduction approaches. This set of measures directly addresses the concerns raised in prior discussions by ensuring that quality measures are tailored to the specific challenges faced by patients and communities, accounting for factors such as patient preferences, health disparities, and access to care. The second project of the QM2 involves revising a patient-reported outcome measure for substance use disorder that was previously developed by our team. This measure is designed to capture the patient’s own perceptions of their treatment experience, including their satisfaction, engagement, and perceived outcomes. It will be refined to better reflect the diverse experiences of individuals in the treatment system, helping to assess the effectiveness of person-centered care strategies. The revised measure will play a crucial role in the QM2 study by offering insights into how well the treatment system aligns with patient needs, preferences, and goals, thereby guiding future improvements in care delivery.

This protocol pertains to the third project, which involves a stepped-wedge clinical trial. It will examine the impact of the QM2 study, incorporating new and revised measures developed in the first two projects. This study is registered on ClinicalTrials.gov under the identifier NCT06408233.

We will initiate a stepped wedge randomized controlled trial involving 1) 35 clinics receiving a performance coaching intervention and 2) a treatment as usual (TAU) condition for all clinics not participating in the intervention. Additionally, qualitative interviews with stakeholders and surveys of all 550 outpatient clinics will be conducted at three different points in time (years 1, 3, and 4). We will use administrative data from 2021–2027, including records from the Office of Addiction Services and Supports (OASAS) treatment registry, Medicaid, and vital statistics, to monitor client outcomes. This concurrent mixed-methods study [94] will evaluate the impact of the OASAS QM2 strategy on patient outcomes and statewide stakeholders, focusing on retention in care and adverse events (emergency department visits, hospitalizations, and mortality). Clinics will be randomized to one of five sequences, varying the timing of the intervention between years 2 and 4.

## Materials and methods

### Project 3 aims: Conduct a stepped-wedge trial that includes two conditions: 1) 35 clinics receiving a performance coaching intervention and 2) a treatment as usual (TAU) condition for all clinics not participating in the intervention to examine the effect of the OTP intervention on THD, retention in care, and adverse events

The SPIRIT checklist was used as a guide for reporting this study protocol (Fig 1). To assess the impact of the OASAS QM2 strategy on care retention and adverse events using a stepped-wedge, mixed-methods design across SUD treatment clinics. Clinics will be recruited to participate in this stepped wedge trial by State partners via email invitations, announcements via State listservs, and announcements at relevant meetings to contact the Project Manager or the Principal Investigators. A total of 35 clinics will be recruited after October 2025. The aim of the intervention is to help clinical staff interpret their quality measures and implement subsequent quality improvement efforts through facilitators. The intervention will be six months long for each clinic and be informed by the i-PARIHS model [95].

**Fig 1 pone.0330882.g001:**
[figure not shown]
SPIRIT diagram for the QM2 Study.

i-PARIHS posits that optimal implementation occurs when practice facilitation promotes the acceptance and use of a new practice innovation by tailoring it to the recipient’s specific needs [95,96]. Facilitators are the active ingredient that help navigate individuals and teams through complex change processes by addressing a) the innovation’s degree of fit within the existing practice, b) the motivations, beliefs, goals, characteristics, and resources of the intervention recipients, and c) the inner and outer context in terms of leadership support, culture, past innovation experiences, the learning environment, organizational priorities, capacity for change, regulatory/policy drivers, incentives/mandates, and system stability/instability. Facilitators or coaches will support clinic staff examination and interpretation of the quality measures and encourage systematic adjustments to clinical and program procedures and workflows to improve care. The coaches will be trained social workers and are trained in quality improvement practices and data management as well as relevant clinical topics and will receive regular supervision by the study team. Specifically, coaches will facilitate: 1) Understanding, visualizing, and utilizing data to monitor system change and create measurable impact; 2) Providing patient-centered care, conducting patient-centered consultations and matching interventions to patient preferences, values, and goals; 3) Incorporating harm reduction strategies for SUD treatment programs; and 4) Using a patient monitoring tool for measurement-based care. The coaches will also be involved in creating training modules for the intervention.

Before the trial begins, clinics receiving the QM2 intervention will be randomized into six cohorts of six-month long interventions over three years. Clinics are randomized to onset of intervention in one of six time periods over the three years of the intervention rollout (years 2–4 of the project) and tracked using administrative data. Administrative data will be used for all clinic clients during each of the seven six-month periods (n ≈ 350/clinic) will be drawn from administrative data. The first six-month period will be a baseline prior to any intervention. Six clinics will be assigned randomly to one of six time periods for onset of intervention. Using administrative data, we will track clients within each clinic over four years, including a pre-intervention six-month baseline period. During the same four-year period, clients in clinics not participating in the stepped-wedge trial will be tracked to better understand changes in outcomes under treatment as usual (TAU) and to compare the outcomes of those clinics with clinics receiving the quality management intervention. We anticipate a final study population of approximately 91,000 individuals per year who are receiving treatment from one of the 571 enrolled outpatient substance use treatment programs. Because this is a stepped-wedge trial, all clinics (and as a result all clients within the clinics) will eventually get the intervention, the randomization will have to do with when the clinic is randomized rather than being assigned to a control or intervention group. Fig 2 illustrates the structure of the stepped-wedge trial.

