*Statistical Analyses of the Proposed Stepped-Wedge Trial:* Analyses will begin with examination variable distributions, appropriate transformations, and patterns for, followed by formal imputation methods if needed [110–112]. We will use Generalized Linear Mixed Models (GLMM) for the stepped-wedge design [106].

*Power Analysis for Primary Outcome Statistical power:* Power estimation for specific outcomes was conducted using PASS 2022 software and Monte Carlo simulation [113]. Sample size and baseline rates (μ) were estimated using administrative data. For 80% power, α = 0.05, ICC = 0.05, and a 5-crossover-point stepped-wedge-RCT with 7 clinics starting at each point, power calculations indicate 80% power to detect a small decrease (RR = 0.93) in adverse events with 35 clinics and 350 clients per clinic per 6-month period (n ≈ 73,500 total observations). This corresponds to a decrease from 0.23 to 0.21 events per 6 months. In racial/ethnic subgroups (10% of clients, n ≈ 35 per site), power remains 80% to detect a modest decrease (OR=0.78), from 0.23 to 0.18.

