### Status and timeline

The stepped-wedge trial is projected to begin in July, 2025. We anticipate completing participant recruitment by October 2025, data collection by December 2026, and expect to have preliminary results available by August 2027.

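### The stated calendar cannot hold the stated stepped wedge, and the power depends on how many starts the outcome data will cover

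*Protocol article*

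**What the plan says.** Materials and methods, Project 3 aims (the randomisation paragraph after Fig 1), has clinics "randomized into six cohorts of six-month long interventions over three years" and then states: "Clinics are randomized to onset of intervention in one of six time periods over the three years of the intervention rollout". It adds that "The first six-month period will be a baseline prior to any intervention", counts seven six-month periods in all, and says "we will track clients within each clinic over four years".

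The Introduction gives five sequences instead of six. The power paragraph under Project 3: Stepped-wedge trial also uses five: a "5-crossover-point stepped-wedge-RCT with 7 clinics starting at each point", with 80% power for RR = 0.93 and about 73,500 observations.

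On dates, Status and timeline says "The stepped-wedge trial is projected to begin in July, 2025" and "We anticipate completing participant recruitment by October 2025, data collection by December 2026, and expect to have preliminary results available by August 2027". Project 3 aims places recruitment of the 35 clinics after October 2025. The Introduction says "We will use administrative data from 2021–2027", and the data specification repeats those years.

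**The concern.** In a stepped wedge, the number of starts observed, and how long each is observed, define the randomised comparison. A clinic whose start falls after the last outcome period contributes only control data to the analysis. The article gives a rollout of three years or nearly so and a calendar of a year and a half. A reader therefore cannot tell whether two, three, four or five sequences will inform the effect estimate, or whether the stated power belongs to the trial that will be run. Choosing between five and six sequences does not settle this, because neither fits the stated dates.

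**Working it through.** **1. Time needed**
- Six cohorts: (1 baseline + 6) × 6 months = 42 months.
- Five crossovers: (1 + 5) × 6 = 36 months. The stated observation count confirms that this is the powered design: 35 × 350 × 6 = 73,500.

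**2. Time available**
- July 2025 to December 2026 is 18 months, or three half-years. With the baseline in July–December 2025, starts fall in January and July 2026: two starts, 2 × 7 = 14 clinics. With a baseline from earlier records and a first start in July 2025: three starts, 21 clinics.
- July 2025 to December 2027 is 30 months, or five half-years. With a July–December 2025 baseline: four starts, 28 clinics. A fifth start would fall in January 2028 and a sixth in July 2028. Five starts fit only if coaching begins in July 2025, before the clinics are recruited. Six do not fit either way.

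**3. Reproducing the stated power**

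I used the Hussey–Hughes model on clinic-period means, with fixed period effects and a random clinic effect. Inputs from the power paragraph: 35 clinics in five sequences of seven, m = 350, ICC = 0.05, baseline rate 0.23, RR 0.93 (target rate 0.23 × 0.93 = 0.2139, difference 0.0161). Two-sided alpha of 0.05 is assumed, because the sidedness is not stated.

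- Total variance: 0.23 × 0.77 = 0.1771.
- Between-clinic: τ² = 0.05 × 0.1771 = 0.00886.
- Within-clinic, per clinic-period mean: 0.95 × 0.1771 / 350 = 0.00048.
- V = τ²J + 0.00048·I, where J is a matrix of ones and I the identity. Var(δ) is the last diagonal element of (Σ D′V⁻¹D)⁻¹, where D holds the period indicators and the intervention column.
- Power = Φ(0.0161/SE − 1.96). Detectable RR = 1 − 2.80 × SE/0.23.

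Full design (six periods): SE = 0.00541, so power = Φ(2.98 − 1.96) ≈ 85% and detectable RR = 1 − 2.80 × 0.00541/0.23 = 0.934. This agrees with the stated 0.93 to two decimals.

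**4. The same model cut to the periods that fit**

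The upper end of each power range takes the binary variance at the mean of the two rates.

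| Starts observed | Periods | SE | Power for RR 0.93 | Detectable RR |
|---|---|---|---|---|
| 5 | 6 | 0.00541 | 85% | 0.93 |
| 4 | 5 | 0.00583 | 79–80% | 0.93 |
| 3 | 4 | 0.00672 | 67–68% | 0.92 |
| 2 | 3 | 0.00849 | 47–48% | 0.90 |

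Six cohorts of six give 65–66% with three starts and 44–45% with two. Putting all 35 clinics into only the starts that fit gives 64% and 44%.

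**5. Sensitivity to what else enters the model**
- *TAU clinics.* The quantitative methods plan to add them. Assuming 550 − 35 = 515 clinics with 150 clients per period, power is 85–86% with three starts and 60–61% with two. Across 80 to 350 clients per period it is about 84–87% and 59–62%.
- *Pre-2025 records.* With an assumed eight extra baseline half-years and no TAU clinics, power is 88–89% with three starts and 72–73% with two.
- *Correlation decay.* All figures above assume none. With an assumed cluster autocorrelation of 0.98, the four rows of the table become about 72–73%, 66–67%, 54–55% and 37–38%.

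**The case against.** The strongest reply is that December 2026 need not end the outcome data. Status and timeline states it next to participant recruitment, so it may refer to surveys and interviews. The primary outcomes come from administrative records, stated twice to run to 2027. On that reading four starts are seen, and power is about 79–80%, as claimed. The planned TAU expansion, or records back to 2021, would also bring three starts above 80%. The printed drop from 0.23 to 0.21 is larger than RR 0.93 and would have about 85% power with three starts, though only about 65–67% with two.

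Much of this stands. A reader might infer that only two or three starts can be observed and that the 80% power is lost. The documents do not support that without conditions: it requires outcome data to stop in December 2026, a single baseline period and no TAU clinics. Nor do the dates show that later clinics never receive coaching, since coaching could follow the data cut.

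The reply does not remove the date conflict. Each clinic's interviews come at the end of its six-month coaching, so interviews finished by December 2026 imply coaching begun by about July 2026. Data to the end of 2027 still do not hold six starts, and preliminary results in August 2027 would precede the end of that window. The power paragraph counts 35 clinics and six periods, so its own figure draws on neither TAU clinics nor earlier records. The TAU gain also rests on non-randomised information about time trends. The 12-month outcome window shortens the usable time further.

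**Conclusion.** The contradiction in dates holds on every reading: 42 months (six starts) or 36 months (five) are needed, against 18 months to December 2026 or 30 months to December 2027. The loss of power is conditional. In the 35-clinic, single-baseline model it is negligible against the claimed 80% with four starts, moderate with three (67–68%) and severe with two (47–48%). With TAU clinics or long pre-trial baselines, three starts suffice. Two starts still fall short of 80% when either is added alone. These figures assume two-sided alpha, ICC 0.05 and no correlation decay; the TAU and pre-trial figures also rest on assumed numbers of clinics, clients and periods.

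**What to change.** Reconcile the Introduction, Project 3 aims, the data specification, the power paragraph and Status and timeline on the number of sequences, the recruitment date, the first start and the last outcome period. Then do one of the following:

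- **Extend the dates.** Set the end of data collection, the administrative data window and the results date from the last period of the wedge. With a July–December 2025 baseline, that period ends in June 2028 for five sequences or December 2028 for six, before allowing for the 12-month outcome window.
- **Keep the dates.** State how many starts will be observed, and restate the power or detectable effect for that design, saying whether TAU clinics and pre-trial periods are included. Without them, the detectable RR at 80% power is about 0.93 with four starts, 0.92 with three and 0.90 with two.

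The first option costs later dates and a longer extract of routinely collected data. The second costs a change of wording and possibly a less favourable stated effect.

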If we observe significant treatment effects (e.g., reduced adverse events) from the performance coaching intervention, we will conduct follow-up analyses to strengthen causal inference. Drawing on methods from treatment mechanism research, we will test whether hypothesized mediators (e.g., person-centered care, retention in treatment) are associated with outcomes. We will also examine moderation by population characteristics and regional variation (e.g., gender, location), as well as provider-level differences in implementation. Lagged treatment effects will be assessed using interaction terms between treatment and time since intervention start by cohort. These exploratory analyses will inform interpretation and guide qualitative inquiry.

*Data and specification:*

We will join multiple administrative data sources from New York State for years 2021–2027 to form our analytical dataset. We will use Client Data System (CDS), Medicaid claims, and NYS vital statistics data to form the analytic dataset. The OASAS treatment registry (CDS) will provide extensive clinical data on clients at treatment admission and will include descriptions of providers through the provider data system (PDS). Medicaid will provide medical diagnoses, healthcare services, SUD treatment services, and medication utilization data. The New York State Vital Statistics will be received from the outpatient clinics in the form of all-cause mortality for clients participating in the trial. Additional OASAS data will provide operational and staffing information for each clinic. To date, 75% of clients in the OASAS registry have been linked to Medicaid claims data.

Quality measures from Project 1 will encompass patient, clinic, and organizational factors, including demographics, clinical complexity, substance use patterns, prior healthcare utilization, community access, substance use trends, resources, psychosocial interventions, clinic structure, staffing, and MOUD use and retention. Primary outcomes include adverse events, healthcare utilization, and mortality. Adverse events are defined as SUD-related hospitalizations or emergency department visits, including overdose, within 12 months of treatment entry. Healthcare utilization includes all-cause emergency department visits or hospitalizations within the same timeframe. Mortality will be assessed as all-cause mortality. Outcome variables will be risk-adjusted to account for client health status.

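### The client set covers everyone in care in each half-year, but the primary adverse-event outcome exists only for the first 12 months after treatment entry

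*Protocol article*

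**What the plan says.** The Protocol article describes the client set and the outcome in different units.

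- **Client set.** Materials and methods (the randomization paragraph after Fig 1): "Administrative data will be used for all clinic clients during each of the seven six-month periods", with about 350 per clinic. No restriction to new admissions is given. The same paragraph describes the wider population as "approximately 91,000 individuals per year who are receiving treatment from one of the 571 enrolled outpatient substance use treatment programs".
- **Primary outcome.** Data and specification, under Project 3: Stepped-wedge trial: "Adverse events are defined as SUD-related hospitalizations or emergency department visits, including overdose, within 12 months of treatment entry". For utilization: "Healthcare utilization includes all-cause emergency department visits or hospitalizations within the same timeframe". For death: "Mortality will be assessed as all-cause mortality", with no window there.
- **Abstract.** Methods and analysis lists substance-use-related emergency visits and hospitalizations together with "mortality among patients within the first 12 months after admission to treatment".
- **Power.** The power paragraph uses 35 clinics, 350 clients per clinic per six-month period, about 73,500 observations, and a fall from 0.23 to 0.21 events in six months (RR 0.93).
- **Model.** Quantitative Methods codes exposure by clinic and period, includes an individual random effect, and allows, without requiring, an offset for time at risk related to when treatment began.

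**The concern.** A client set defined by being in care includes people at any distance from admission. An outcome defined from treatment entry applies only to those within 12 months of it. Someone two or three years into treatment belongs to the first and has no adverse-event or utilization outcome under the second. Two analysts, one following the client-set sentence and the other the outcome definition, would build different primary datasets.

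Two further risks depend on how the gap is filled:

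- **Long-stay clients kept and scored as no event.** The rate would then depend on the length-of-stay mix. Retention is a target outcome of the trial and a hypothesized mediator. Coaching that improved retention could therefore lower the rate after crossover without fewer events.
- **A 12-month outcome attached whole to every half-year row.** The window covers two half-years if admission falls on a period boundary and three otherwise. One event could then be counted two or three times, possibly on both sides of a crossover.

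**Working it through.** **1. Reproduce the stated number of observations.** Five crossover points plus baseline give six periods: 35 × 350 × 6 = 73,500, exactly as stated. This needs every one of the 350 to supply an outcome in every period. (The seven periods named in Materials and methods would give 35 × 350 × 7 = 85,750.)

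**2. Reproduce the power.** Method: Hussey–Hughes cross-sectional stepped-wedge variance, client-periods independent within clinic. Inputs from the power paragraph: I = 35 clinics, 7 per crossover, T = 6, m = 350, ICC 0.05, α = 0.05 (two-sided assumed), 0.23 against 0.23 × 0.93 = 0.2139.

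- Mean rate = (0.23 + 0.2139)/2 = 0.22195; σ² = 0.22195 × 0.77805 = 0.1727.
- τ² = (0.05/0.95) × 0.1727 = 0.00909; s = σ²/350 = 0.000493.
- U = 7 × (5+4+3+2+1) = 105; W = 49 × (1+4+9+16+25) = 2,695; V = 7 × (25+16+9+4+1) = 385.
- Var = I·s·(s + T·τ²) / [(IU − W)·s + (U² + ITU − TW − IV)·τ²] = 35·s·(s + 6τ²) / (980·s + 3,430·τ²).
- SE = 0.00548; power = Φ(0.0161/0.00548 − 1.96) = 83.6%.

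The RR detectable with 80% power is 0.933, which rounds to the stated 0.93. The article used PASS and simulation, so the gap between 83.6% and 80% is not called an error.

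**3. Vary the share of the 350 within 12 months of entry.** The documents do not give this share, so the values are assumptions. The rate is held at 0.23 and only m changes. The last column takes the stated fall to 0.21 literally.

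| Share in window | Observations | Power, RR 0.93 | RR detectable at 80% | Power, 0.23 to 0.21 |
|---|---|---|---|---|
| 100% | 73,500 | 83.6% | 0.933 | 95.6% |
| 90% | 66,150 | 79.6% | 0.929 | 93.5% |
| 75% | 55,125 | 72.2% | 0.923 | 88.8% |
| 50% | 36,750 | 55.0% | 0.906 | 73.8% |
| 25% | 18,375 | 31.7% | 0.869 | 45.5% |

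**4. Compare the outcome units.** If 0.23 is read as a six-month risk and half-years are independent, the 12-month risk is 1 − 0.77² = 0.41. The powered quantity and the defined quantity are not the same.

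**5. Conditional repetition.** If one 12-month outcome were repeated unchanged in two or three periods, 73,500 rows would hold 73,500/2 = 36,750 or 73,500/3 = 24,500 distinct outcomes. As a crude bound, power at RR 0.93 would be about 55% or 40%.

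**6. Could the 350 already be new admissions?** The wording does not say so. The article's own figures give 91,000/571 ≈ 159 people in treatment per program per year, well below 350 admissions in six months. Trial clinics may be larger than average, so this is weak support only.

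**The case against.** The strongest defence is that the client-set sentence describes the data extract, while the abstract and the data specification fix the denominator. A client past 12 months would then simply drop out. The per-six-month rate, the individual random effect and the optional offset also fit events split by period, with repeated rows modelled. An article may leave the assignment of events to periods to a fuller document.

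Much of this stands. A reader might infer that the plan counts one outcome in several periods, or that long-stay clients enter as event-free and bias the trial towards benefit by as much as the design effect. The documents support neither. No sentence attaches a whole 12-month outcome to each half-year, and none scores clients past the window as zero. Sizing such a bias would need a long-stay share and a shift in it under coaching, and the article gives neither. The claim is also limited to adverse events and utilization: the data specification puts no window on mortality, although the abstract can be read as giving one.

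The defence does not remove the contradiction. If clients past the window drop out, the 350 and the 73,500 cannot include them, yet both are stated for all clients in every period. The offset does not help: it is optional, and someone past 12 months has no time at risk under the stated definition. If events are counted per six months for everyone in care, the definition of 12 months from entry no longer holds. This is a conflict between stated figures, not a detail left out.

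**Conclusion.** The point holds as a mismatch between analysis set and outcome unit. Taken together, the client-set sentence, the outcome definition and the power paragraph yield either rows with no valid adverse-event outcome, or an n, baseline rate and power that do not apply to the primary outcome as defined.

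The size depends on an undisclosed share. At RR 0.93, power drops just under 80% once about 10% of the 350 fall outside the window, and to about 72% at 25% and 55% at 50%. Taking the stated fall to 0.21 literally, it stays above 80% at 25% and is below it at 50%. These figures assume a two-sided test, ICC 0.05, independent client-periods and a rate fixed at 0.23. A higher 12-month rate at the same RR would recover some power. Entering each admission once would remove more rows than the out-of-window share alone, because an in-window client can be in care in up to three half-years. The table therefore shows sensitivity to n and is not a forecast.

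Repeat counting and a retention-driven fall in the rate remain conditional risks, to be closed off by the same rule.

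**What to change.** State one analysis-set rule that matches one outcome, and make the abstract, Materials and methods, data specification, model and power paragraphs agree with it.

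- **Keeping the stated outcome:** restrict the adverse-event analysis to clients within 12 months of entry. Enter each new admission once, in its half-year of admission, and exclude continuing clients. State how exposure is assigned when the 12 months run across the clinic's crossover, since this rule alone does not settle that.
- **If a six-month outcome for everyone in care is intended:** redefine adverse events and utilization that way in the abstract and data specification, and say that each event is counted only in the half-year in which it occurs.

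Under either choice, state the mortality window. Recount clients per clinic-period from the registry, and restate the baseline rate, total observations and power on that basis.

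The cost is a paragraph of specification, a registry count and a rerun of the power calculation. Under the first option, n falls and the stated power may become less favourable. The second option keeps the 350 but changes the declared primary outcome. The Ethics approval section dates research access to the retrospective data from 1 October 2025, so the rule is best fixed before outcomes are examined.
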